### 6.3.1.2 Hepatotoxicity

Immune-mediated hepatitis has been associated with the administration of atezolizumab.

While on this study, patients presenting with right upper-quadrant abdominal pain and/or unexplained nausea or vomiting should have liver function tests (LFTs) performed immediately and reviewed before administration of the next dose of study drug.

If LFTs increase, neoplastic, concurrent medications, viral hepatitis, and toxic etiologies should be considered and addressed as appropriate. Imaging of the liver, gall bladder, and biliary tree should be performed to rule out neoplastic or other causes for the increased LFTs. Anti-nuclear antibody, perinuclear anti-neutrophil cytoplasmic antibody, anti-liver kidney microsomal antibody, and anti-smooth muscle antibody tests should be performed if an autoimmune etiology is considered.

Patients with liver function test (LFT) abnormalities should be managed according to the guidelines in table 2.

**Table 2: Guidelines for Managing Atezolizumab-Associated Hepatotoxicity**

| LFT Abnormalities                                                                                    | Management                                                                                                                                                                                                                                                                                                                                                                                                                                                                                                                                                                                                                                                                                                                                                                                                                                                                                                                                                                                                                |
|------------------------------------------------------------------------------------------------------|---------------------------------------------------------------------------------------------------------------------------------------------------------------------------------------------------------------------------------------------------------------------------------------------------------------------------------------------------------------------------------------------------------------------------------------------------------------------------------------------------------------------------------------------------------------------------------------------------------------------------------------------------------------------------------------------------------------------------------------------------------------------------------------------------------------------------------------------------------------------------------------------------------------------------------------------------------------------------------------------------------------------------|
| Grade 1
ASAT/ALAT (> ULN to $3 \times$ ULN) with total bilirubin > ULN to $1.5 \times$ ULN | 

Continue atezolizumab.

Continue with the standard monitoring plan

                                                                                                                                                                                                                                                                                                                                                                                                                                                                                                                                                                                                                                                                                                                                                                                                                                                                                                 |
| Grade 2
ASAT/ALAT (> $3$ to $5 \times$ ULN with total bilirubin > $1.5$ to $3 \times$ ULN  | 

Continue atezolizumab.

Monitor LFTs at least weekly until return to baseline values.

If persists > 5-7 days: hold atezolizumab and start 60 mg prednisone or equivalent per day, when LFTs <math>\leq</math> G1, taper steroids over <math>\geq 1</math> month, resume therapy when systemic steroid dose is <math>\leq 10</math> mg oral prednisone equivalent per day.

Consider GI consult

                                                                                                                                                                                                                                                                                                                                                                                                                                                                                                                                                   |
| Grade 3
ASAT/ALAT > $5$ to $20$ ULN
Total Bilirubin > $3$ to $10 \times$ ULN            | 

Hold atezolizumab.

Consult hepatologist and consider liver biopsy to establish etiology of hepatic injury if necessary.

Start IV steroids (60 mg prednisone or equivalent per day) for 24–48 hours followed by oral prednisone (or equivalent) taper over 2–4 weeks.

If LFT results do not decrease within 48 hours after initiation of systemic steroids, addition of an alternative immunosuppressive agent (e.g., mycophenolate 1000 mg BID orally, taper after 2 weeks) to the corticosteroid regimen may be considered.

Monitor LFTs every 48–72 hours until decreasing and then follow weekly.

Restart atezolizumab after discussion with the PI if ASAT/ALAT <math>\leq 3 \times</math> ULN with bilirubin < <math>2 \times</math> ULN and steroid dose is <math>\leq 10</math> mg oral prednisone equivalent per day.

Permanently discontinue atezolizumab for life-threatening immune-related hepatic events.

 |
| Grade 4
ASAT/ALAT $\geq 20 \times$ ULN with bilirubin > $10 \times$ ULN                    | 

Hold atezolizumab.

Consult hepatologist and consider liver biopsy to establish etiology of hepatic injury if necessary.

Start IV steroids (60 mg prednisone or equivalent per day) for 24–48 hours followed by oral prednisone (or equivalent) taper over 2–4 weeks.

If LFT results do not decrease within 48 hours after initiation of systemic steroids, addition of an alternative immunosuppressive agent (e.g., mycophenolate 1000 mg BID orally, taper after 2 weeks) to the corticosteroid regimen may be considered.

Monitor LFTs every 48–72 hours until decreasing and then follow weekly.

Permanently discontinue atezolizumab for life-threatening immune-related hepatic events.

                                                                                                                                                                                                                                     |

IV = intravenous; LFT = liver function test; TNF- $\alpha$  = tumor necrosis factor alpha; ULN = upper limit of normal.

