- For patients with Grade 2 AST/ALT, and/or alkaline phosphatase abnormality at baseline, an increase to  $\geq 10 \times$  the upper limit of normal (ULN) that does not resolve to Grade  $\leq 2$  within 48 hours (if symptomatic) or that does not resolve to Grade  $\leq 1$  within 3 weeks of onset (if asymptomatic) will be considered a DLT after AST/ALT elevation due to disease progression has been ruled out
- Grade  $\geq 3$  pneumonitis
- Grade  $\geq 3$  colitis

Failure to recover from any toxicity that results in a delay of 2 scheduled administrations of atezolizumab is considered a DLT. The following are not considered DLTs:

- Grade  $\geq 3$  nausea, vomiting, or diarrhea that resolves to Grade  $\leq 1$  with or without treatment prior to the next infusion

- Grade  $\geq 3$  immune-related adverse event that resolves to Grade  $\leq 1$  with immunosuppressant therapy within 3 weeks of its onset
- Grade  $\geq 3$  fatigue that resolves to Grade  $\leq 2$  within 1 week
- Grade  $\geq 3$  arthralgia that can be adequately managed with supportive care or that resolves to Grade  $\leq 2$  within 1 week
- Grade  $\geq 3$  hypophosphatemia reversible to  $<$  Grade 2 within 1 week
- Grade  $\geq 3$  laboratory abnormality that is asymptomatic and deemed by the investigator not to be clinically significant
- Grade  $\geq 3$  autoimmune thyroiditis or other endocrine abnormality that can be managed by endocrine therapy or hormonal replacement
- Grade  $\geq 3$  tumor flare defined as local pain, irritation, or rash localized at sites of known or suspected tumor
- Alopecia (any grade)
- Infusion related reactions (IRRs): IRRs are not considered to be DLTs because based on experience with monoclonal antibodies; IRRs are not dose-related events. Precautions will be taken if IRRs Grade  $\geq 2$  occurs. If described precautions are not sufficient, other options will be discussed between the sponsor and the investigator.

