- ◆ Bilirubin  $< 1.5 \times$  upper limit of the normal range (ULN), except subjects with Gilbert Syndrome; alkaline phosphatase  $< 2.5 \times$  ULN ( $< 5 \times$  ULN in case of liver metastases, and  $< 7 \times$  ULN in case of bone metastases); transaminases (ASAT/ALAT)  $< 3 \times$  ULN (and  $< 5 \times$  ULN in case of liver metastases), **LDH  $< 2 \times$ ULN**.
- ◆ Serum creatinine  $\leq 1.5$  ULN or calculated (Cockcroft-Gault) or measured creatinine clearance  $> 40$  mL/min
- ◆ Evaluable disease or measurable according to RECIST 1.1
- ◆ Subjects with brain metastases are eligible if they have been treated, are not symptomatic and there is no magnetic resonance imaging (MRI) evidence of progression for at least 28 days prior to first dose of study drug administration. There must also be no requirement for immunosuppressive doses of systemic corticosteroids ( $> 10$  mg/day prednisone equivalents) for at least 2 weeks prior to study drug administration
- ◆ No known leptomeningeal disease localization
- ◆ No history of having received other anticancer therapies within 2 weeks of start of the study drug
- ◆ No history of immunodeficiency, autoimmune disease, conditions requiring immunosuppression ( $>10$  mg/day prednisone or equivalent) or chronic infections. Subjects with vitiligo, diabetes mellitus type I, psoriasis not requiring systemic treatment or resolved childhood asthma/atopy would be an exception to this rule. Subjects that require intermittent use of bronchodilators, inhaled steroids, or local steroid injections would not be excluded from the study. Subjects with hypothyroidism stable on hormone replacement, Sjögren's syndrome or conditions not expected to recur in the absence of an external trigger will not be excluded from the study. Adrenal replacement doses  $>10$  mg/day prednisone or equivalent are permitted in the absence of active autoimmune disease
- ◆ No prior treatment with immune checkpoint blockade such as but not limited to anti-PD(L)1, anti-PD-L2, anti-CTLA-4, anti-GITR or CD137/OX40-agonist

- ◆ No live vaccine within 2 weeks prior to start of study, at any time during the study, or within 5 months following the last dose of atezolizumab. Inactivated vaccines are allowed
- ◆ No active other cancer

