#### Other toxicities

If the patient develops any other grade 3 or 4 toxicity thought to be related to carboplatin, carboplatin should be held until symptoms resolve to ≤ grade 1 or baseline (atezolizumab treatment should continue as scheduled).

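### Hepatotoxicity Table 2: at grades 3 and 4 the steroid taper starts after 24–48 hours with no liver-function condition, although persistent grade 2 and every other stated taper rule wait for improvement

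*Protocol*

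**What the plan says.** Section 6.3.1.2 directs that patients with LFT abnormalities be managed by its Table 2. Three rows use systemic steroids, all at 60 mg/day prednisone or equivalent.

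- **Grade 2 persisting beyond 5–7 days:** "hold atezolizumab and start 60 mg prednisone or equivalent per day, when LFTs" are at or below G1, taper over at least 1 month. The row also says "Monitor LFTs at least weekly until return to baseline values".
- **Grade 3 and grade 4 (same wording in both rows):** IV steroids for 24–48 hours, "followed by oral prednisone (or equivalent) taper over 2–4 weeks".

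The grade 3 and 4 rows mention LFTs in two further places: a monitoring schedule (every 48–72 hours until decreasing, then weekly) and a rescue step, "If LFT results do not decrease within 48 hours after initiation of systemic steroids, addition of an alternative immunosuppressive agent" to the corticosteroid regimen, which may be considered. The grade 3 row also sets LFT limits for restarting atezolizumab. None of these is tied to the taper.

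**The concern.** At one starting dose, the milder event keeps its steroid until the liver has recovered, while the more severe event moves to a taper by the calendar. A site following the table literally would begin withdrawing steroid at grade 3 or 4 after one or two days, whether or not LFTs had responded, and could finish in about two weeks. What is at stake is control of a severe immune-mediated hepatitis in the few patients who develop one. Sample size, error rates and the primary analysis are not involved.

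**Working it through.** The protocol gives no figure to reproduce, so the check sets its rules side by side and adds simple duration arithmetic.

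**1. The three steroid rows of Table 2**

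| | Persistent grade 2 | Grades 3 and 4 |
|---|---|---|
| Daily dose (prednisone equivalent) | 60 mg | 60 mg, IV at first |
| Taper starts | when LFTs are at or below G1 | after 24–48 hours |
| Taper length | at least 1 month | 2–4 weeks |
| LFT condition on taper | yes | none |

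**2. Durations** (taking 1 month as 30 days; T = days to reach grade 1, which the protocol does not give)

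- Taper length: 14–28 days at grades 3–4, at least 30 days at grade 2. Difference: 30 − 28 = 2 to 30 − 14 = 16 days.
- End of course from first dose: 1 + 14 = day 15 to 2 + 28 = day 30 at grades 3–4; T + 30 days or later at grade 2.
- Taper start relative to the 48-hour LFT result: 48 − 48 = 0 to 48 − 24 = 24 hours before it.

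**3. Does the 48-hour step supply the missing condition?** It permits a second agent and does not say whether the taper pauses. The example given, mycophenolate, is itself timed: tapered after 2 weeks, so from about day 2 + 14 = 16 if added at 48 hours. By contrast, colitis Table 1 answers non-response to prednisone by adding infliximab and says explicitly that prednisone continues.

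**4. Comparison with the other toxicity tables in section 6.3.1.** Systemic-steroid taper rules:

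| Table | Rules | Wait for improvement |
|---|---|---|
| 1 Colitis (after prednisone; after infliximab) | 2 | 2 |
| 2 Liver (grades 2, 3, 4) | 3 | 1 |
| 4 Endocrine | 1 | 1 |
| 5 Pulmonary (grade 2; grades 3–4) | 2 | 2 |
| 6 Pancreatic (raised enzymes; pancreatitis) | 2 | 2 |
| 7 Eye (grades 3–4) | 1 | 1 |
| 10 Myositis (grade 4) | 1 | 1 |
| **Total** | **12** | **10** |

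Grade 3 rash and grade 2–3 myositis state no taper rule. The only other taper shorter than 4 weeks, colitis after infliximab, requires improvement and follows an added agent.

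**5. Can every patient reach grade 1?** This matters for the wording of a fix. In Table 2, grade 1 ends at 3 × ULN for ASAT/ALAT and 1.5 × ULN for bilirubin. Section 5 raises the transaminase limit to below 5 × "ULN in case of liver metastases", and sets the bilirubin limit "except subjects with Gilbert Syndrome". A patient enrolled at 4 × ULN could recover fully to baseline and never reach grade 1. The protocol recognises such patients elsewhere: section 4.2 has a rule "For patients with Grade 2 AST/ALT, and/or alkaline phosphatase abnormality at baseline", and section 6.3.2 says "carboplatin should be held until symptoms resolve to ≤ grade 1 or baseline".

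**6. Patients affected.** Section 6.1.1 reports related grade 3 events in 412 monotherapy patients: autoimmune hepatitis in 3, raised AST in 4, raised ALT in 4.

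- Hepatitis alone: 40 × 3/412 = 0.29.
- All 11 reports in different patients: 40 × 11/412 = 1.07.

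Rates with weekly carboplatin are not given.

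**The case against.** The best defence is that the two pathways are not like for like. The grade 2 rule covers only events that persist for days before steroids begin. Grades 3–4 get immediate IV treatment, a hepatologist consult, possible biopsy, frequent LFTs and an optional second agent. Section 6.3.1 calls the tables guidance and refers to standard medical practice, so a specialist with serial LFTs in hand may hold the taper. The range also permits 4 weeks, which is about 1 month.

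Most of this stands and limits the weight of the point. Care does escalate with grade, and the length contrast is weak at its upper end. The gap of up to 24 hours before the 48-hour result carries little weight, because no taper steps are given and the first oral dose may still be near 60 mg. What does not stand is that these features replace the missing condition: latitude to hold the taper is not an instruction to do so.

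Two stronger readings are tempting. One is that the table requires steroid withdrawal while LFTs rise; it is silent there, and section 6.3.1 leaves room for judgement. The other is that the short taper exposes patients to early re-challenge. After grade 3, restart needs ASAT/ALAT at or below 3 × ULN, bilirubin below 2 × ULN, prednisone at or below 10 mg/day and discussion with the principal investigator, so a short taper alone does not lead there. Nor do the documents show that a monitored 2–4 week taper causes relapse; the argument here is internal consistency.

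**Conclusion.** The point holds as a minor patient-safety inconsistency. The grade 3 and grade 4 liver rows are the only 2 of 12 stated systemic-steroid taper rules without an improvement condition, and they sit beside a grade 2 row that has one at the same dose. The missing condition is the substance; the 2–16 day shorter taper is secondary. The expected number affected is roughly 0–1 of 40. That assumes the monotherapy grade 3 rates carry over to the combination, and its upper end assumes no overlap between the AST, ALT and hepatitis reports. No statistical quantity changes.

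**What to change.** In both the grade 3 and grade 4 rows of Table 2, keep the 24–48 hour IV period and replace the taper text with: convert to oral prednisone 60 mg/day or equivalent; do not start the taper until LFTs are falling, and once they are at or below grade 1 or back to baseline, taper over at least 1 month. The baseline alternative is needed for patients enrolled above the grade 1 ceiling. If a smaller edit is preferred, add one sentence to each row: the taper does not start until LFTs are falling. Adding the baseline alternative to the grade 2 row is optional.

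The cost is an edit to two table rows and somewhat longer oral steroid exposure: a taper at least 2–16 days longer, plus the wait for recovery. Where tumour rather than immune injury drives the LFTs, that wait could be long, so the work-up for other causes in section 6.3.1.2 should guide whether steroids continue. Restart after grade 3 may come later. Section 6.3.1 already allows atezolizumab to be held beyond 42 days for a steroid taper, by agreement between the investigator and the principal investigator, so discontinuation is not forced. The restart limits stay as they are; a patient whose baseline ASAT/ALAT exceeds 3 × ULN could therefore complete the taper and still not meet them.

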### 6.3.1.3 Dermatologic toxicity

Treatment-emergent rash has been associated with atezolizumab. The majority of cases of rash were mild in severity and self-limited, with or without pruritus. A dermatologist should evaluate persistent and/or severe rash or pruritus. A tissue sample should be collected for biopsy unless contraindicated.

Dermatologic toxicity and rash should be managed according to the guidelines in Table 3.

**Table 3. Guidelines for Managing Atezolizumab-Associated Dermatologic Toxicity**

| Dermatologic Toxicity/Rash (e.g., Maculopapular or Purpura) | Management                                                                                                                                                                                                                                                                                                                                                                                                                                                                                                    |
|-------------------------------------------------------------|---------------------------------------------------------------------------------------------------------------------------------------------------------------------------------------------------------------------------------------------------------------------------------------------------------------------------------------------------------------------------------------------------------------------------------------------------------------------------------------------------------------|
| Grade 1, mild, < 10% BSA                                    | 

• Continue atezolizumab.

• Administer symptomatic therapy with antihistamine PRN.

• Consider topical steroids and/or other symptomatic therapy (e.g., antihistamines).

                                                                                                                                                                                                                                                                        |
| Grade 2, moderate, 10%–30% BSA                              | 

• Continue atezolizumab.

• Consider dermatologist referral.

• Administer symptomatic therapy with antihistamine PRN.

• Administer topical steroids.

• Consider higher potency topical steroids if rash unresolved.

                                                                                                                                                                                                            |
| Grade 3, severe, > 30% BSA                                  | 

• Hold atezolizumab.

• Consult dermatologist.

• Administer higher potency topical steroids

• Administer symptomatic therapy with antihistamine PRN.

• If no effect: Administer oral prednisone 10 mg or equivalent. If rash unresolved after 48–72 hours, administer oral prednisone 60 mg or equivalent.

• Restart atezolizumab if rash resolved and systemic dose is ≤ 10 mg oral prednisone or equivalent per day.

 |
| Grade 4                                                     | 

• Permanently discontinue atezolizumab for life-threatening immune-mediated dermatologic toxicity

• Contact PI's if atezolizumab is discontinued.

                                                                                                                                                                                                                                                                                                     |

BSA = body surface area; PRN = as needed.

### 6.3.1.4 Endocrine toxicity

Thyroid disorders, hypophysitis and adrenal insufficiency have been associated with the administration of atezolizumab. Patients with unexplained symptoms such as fatigue, myalgias, impotence, mental status changes, or constipation should be investigated for the presence of thyroid, pituitary, or adrenal endocrinopathies, as well as for hyponatremia or hyperkalemia. An endocrinologist should be consulted if an endocrinopathy is suspected. TSH and free T4 levels should be obtained to determine whether thyroid abnormalities are present. TSH, prolactin, and a morning cortisol level will help to differentiate primary adrenal insufficiency from primary pituitary insufficiency. Endocrine toxicity should be managed according to the guidelines in Table 4.

